#### **D. 11. Ethical Considerations**

All of the communities will be covered by the PCI program in a staggered approach providing the setting of a natural experiment for the study. Thus, every household will have access to the SODIS technology by the end of the program. Each village will be informed about the date of the forthcoming implementation of the SODIS intervention, i.e. villages in the control arm of the trial will know and have agreed upon their "delayed-intervention" status. Compensatory actions or resentful demoralization due to differential treatment of intervention and control villages are thus not an issue of concern. The selected communities will be informed through their village government who meet regularly with the PCI representatives, about the background of the study in broad terms. The village government as well as the community representatives must have given their consent for the whole project. Children will be enrolled in the study following written informed consent of both of their parents (Appendix M). Withdrawal from the trial is possible at any time without any consequences for the child, family and household. All information obtained from the questionnaires will be treated as strictly confidential and will not be passed to any other person or institution outside the research team. All children identified during any survey as suffering from a severe form of diarrhea (fever and/or signs of dehydration present) will be referred to the nearest health facility. Health service delivery to the study participant is provided through the regular health care system. Treatment is provided free of charge and is organized through the office of the District Medical Officer (DMO) together with the district health team. The project team is not involved in any patient

care. However, as services of local health posts are often interrupted due to delayed or inadequate supply of drugs our project will make budgetary provisions to support the local health posts in the project area to ensure these services to the study participants.

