#### **B.4. Significance of gastrointestinal infections in Bolivia; rationale for specific pathogen testing**

General. Diarrheal disease account for nearly 20% of the deaths in children below five years of age in Latin America (Murray and Lopez 1994). In 1998, Bolivia developed a program for epidemiological surveillance as well as a health information system to detect changes in the state of health of the population. Data from a national survey from 1994 indicate a two week prevalence of diarrhea of 29.9% for children under five with little differences between urban and rural settings (30.9% vs. 28.7%). The same source reports a two-week prevalence of bloody diarrhea of 4.4% in urban and 7.7% in rural settings ( $p<0.0001$ ) (ENDSA, 1994/S.I.N.S.). One local hospital-based empiric study indicated that 20% of patients presenting with diarrhea required admission and they estimated a diarrhea-attributable mortality of 7% (Ise et al. 1994). We obtained data for the Cochabamba region that indicate acute diarrhea incidence rates ranging from 16.5% – 37.8% in children under five which are consistent with these high rates (S.N.I.S, Sistema Nacional de Informacion de Salud).

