Bacterial agents. *Salmonella*, *Shigella*, *Campylobacter* and different strains of enteropathogenic *E.coli* are the most common causes of bacterial diarrhea: Only a small number of hospital-based studies report pathogen-specific findings: A study in patients from La Paz, Santa Cruz and Cochabamba investigated the etiology of bloody diarrhea and identified a bacterial agent in 41% of the 133 cases with *Shigella* sp being the most frequent agent diagnosed in 29% of the specimen, *Campylobacter* sp in 9%. *S. flexneri* was the most frequent of the isolates (72%). Enteropathogenic *Escherichia coli* strains were not investigated (Townes et al. 1997). The more comprehensive bacteriological study by Utsunomiya et al. in La Paz and Sucre isolated enteropathogenic *E.coli* strains in 18% of the cases (N=1234) and low prevalence of *Shigella* sp (6%), *Salmonella* sp (3%) and *V.cholerae* (3%) (Utsunomiya et al. 1995). In our pilot study for this project we found similarly low prevalences of these organisms, approximately 5% (Section C and Appendix F). These studies indicate the importance of bacterial infections among symptomatic cases. One local Bolivian community-based study confirms these findings and found a prevalence of 28% for bacterial agents in diarrheal cases with *Campylobacter* and enterotoxigenic *E.coli* (ETEC). This study also identified rotavirus in 6.2% of their sample. A study in neighboring Brazil identified enteropathogens in more than 50% of all symptomatic cases and in 17% of healthy control patients recruited from pediatric clinics (Seigel et al. 1996).

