| Kuri (alto, centro) | 8                     | 5 (62.5%)  | 22.4        | 35.8                 | 75.6    | 9 (river bed)           |
| Vina Perdida        | 10                    | 10 (100%)  | 209.6       | 209.6                | 476.4   | 34 (irrigation channel) |
| Lampesillos         | 9                     | 2 (22.2%)  | 22.8        | 102.5                | 137.9   | 0 (spring-tank)         |
| Yunguillas          | 3                     | 3 (100%)   | 76.0        | 76                   | 45.3    | 1 (irrigation channel)  |

( ) Percent cfu measurements >0 cfu /100ml

\* mean of three repeated measurement per type of community water source (in brackets)

Water was reported to be collected on average 4 times per day, mainly in buckets (74.5%) and small canisters (17%) and more than 60% of all households were storing drinking water for more than 24 hours.

- *Ethnomedical concepts of child diarrhea* : We conducted a qualitative assessment to culturally adapt our instruments and to understand child diarrheal illness in the local Quecha context and to facilitate addressing the topic in our interviews. This exploration revealed nine different terms and local beliefs about etiology and treatment. “Kechalera” is the general term in the quechua language for liquid stool. Sub types specify bloody, mucoid and prolonged diarrheas (Appendix F, Table 3.). The ethnomedical terms are today considered as well defined entities in the traditional culture of the Quechua, but without a specific equivalent in the biomedical pathology. Ongoing analysis will determine those terms for inclusion in the survey instruments that most closely resemble biomedically defined diarrhea.

- *Monitoring the use of SODIS* : For monitoring the use of SODIS a radiation-sensitive, color-fading marker will be further developed as a practical technical monitoring tool (see above). In addition, SODIS users and defaulters, those who abandon the use of solar disinfection, will be surveyed individually and in groups to provide insights in motives and determinants (supportive and negative) of the SODIS method (Appendix J). These series of individual case studies and group discussions will generate valuable information to improve the effectiveness of the SODIS Program.

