## D.4. Definition of diarrhea (principal outcome)

An episode of diarrhea will be defined in this activity and throughout the trial as a 24 hours period with three or more non-bloody loose or liquid motions, or one or more bloody, loose or liquid motions and three diarrhea-free days between a new onset. This is in concordance with the WHO recommendations and recent research (Ahmed et al. 1994, Aziz et al. 1990, Morris et al. 1994) and allows the comparison with other studies on diarrheal diseases in developing countries. Concepts of diarrheal illness and disease differ within and between cultures (Pitts et al. 1996, Weiss 1988). For example, a nutritional program in Honduras neglected to use word 'empacho' in their instructions for correct feeding practices of diarrheal cases. The subsequent inclusion of the folk term significantly improved the program's impact (Scrimshaw and Hurtado 1988). Attempts will be made during the pilot phase to assess the cultural perception of diarrheal illness and to elucidate the folk terminology and basic local illness beliefs about diarrhea (Appendix L). We conducted similar studies in previous research to obtain and validate local folk terms for diarrheal illness that resemble most closely the biomedical definition for diarrheal illness mentioned previously (Mausezahl 1996, Pitts et al. 1996).

A start of a new episode of diarrhea will be defined as the first day of diarrhea that occurs after at least three consecutive diarrhea-free days. Similarly, the end of an episode is determined by the onset of three consecutive diarrhea-free days. Our choice of three rather than some other number of disease-free days is based on the work of Morris *et al* who modelled the sensitivity of different definitions of diarrheal episodes and described the definition we

have chosen as ideal in situations of medium to high incidence (specifically greater than six trigger events/child/year) allowing for different lengths of duration and within-child clustering (Morris et al. 1994). Persistent diarrhea is defined as an episode lasting longer than 14 days according to WHO standards (Anonymous 1988); diarrhea episodes of shorter duration will be defined as "acute".

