#### **D.6. c. Determining the monthly incidence of child diarrhea in both arms of the study**

This task will be achieved by monitoring diarrheal morbidity in a cohort of 30 study children (from different households) in each of the 22 village-clusters, (total of 330 children in each study arm, 660 children total). We will obtain information on our main outcome, cluster(village)-level incidence rates of diarrheal episodes through two monitoring procedures for the entire 12 month follow-up period:

- 1.) Morbidity diaries: Morbidity calendars will be kept by mothers/caretakers of the children. The use of morbidity diaries or 'illness calendars' has recently been reviewed and their usefulness and validity confirmed in prospective studies on child health (Goldman et al. 1998). The mother/caretaker will be given a simple morbidity calendar to keep daily records of the child's morbidity status. This chart was pre-tested among 11 households in our pilot study in Mizque and the graphical illustrations proved culturally valid. The number of bowel movements (from sunrise to sunset), color and consistency of the stool as well as specific symptomatic features of the diarrheal episode were recorded using colored stickers (Appendix J). The usefulness of the tools for monitoring child health has been taken up enthusiastically by mothers and quantitative data on diarrhea frequency were collected (Jul-Aug.2002) in one village.
- 2.) Weekly home visits by community-based fieldworkers. Specific inquiries about the occurrence of a diarrheal episode using a standardized questionnaire will be made at the time of the fieldworker's weekly home visit. We will use vernacular terms of locally defined diarrheal illnesses derived from ethnographic pilot investigations in Mizque. For each of those illnesses, we will assess indicators for diarrhea as objectively as possible. This includes frequency of bowel movements and the presence of other symptoms (fever, vomiting, dehydration). Signs of dehydration will be assessed by both the number of urinations in last 24 hours as well as by capillary refill time. The different outcomes of the study (see below) will, thus be obtained by 52 measurements during the 12 months of follow-up. The assessment of the impact of SODIS on diarrheal morbidity will be obtained from cluster-level (villages) and individual (child) level outcome measures:

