Village-level outcome measures: a *cluster(village)-level incidence rate* will be obtained by dividing the total number of diarrheal episodes in a cluster (village) by the total observation time of the study children in each village. This represents an incidence density measure. Similarly, the *mean number of episodes* of diarrhea per village-cluster will be compared among study groups.

Child-level outcome measures: the *total number of days with diarrhea*, and the *mean duration of diarrhea*, and the *number of visits to a healthcare provider* will be used for a child-level analysis of the intervention effect. The impact of

SODIS in terms of reduction of severe diarrheal episodes with blood, and/or fever or persistent episode (>14 days) will be assessed in a separate analysis.

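### The D.11 referral rule names only fever and dehydration, so a child with bloody stool or diarrhea beyond 14 days but neither sign has no stated referral trigger

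*Protocol*

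**What the plan says.** D.11 (Ethical Considerations) sets the rule: "All children identified during any survey as suffering from a severe form of diarrhea (fever and/or signs of dehydration present) will be referred". The bracket is the working definition of severe. The same section says that treatment comes free through the regular health system, that the project team gives no patient care, and that the project budgets support for health posts because their services are often interrupted.

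D.6.c uses a different notion of severity for analysis: the effect on "severe diarrheal episodes with blood, and/or fever or persistent episode (>14 days) will be assessed in a separate analysis". D.4 counts a day as diarrhea on three or more non-bloody loose motions "or one or more bloody, loose or liquid motions", and it calls an episode longer than 14 days persistent.

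On data collection, D.6.c says of the weekly visit: "This includes frequency of bowel movements and the presence of other symptoms (fever, vomiting, dehydration"). Of the pre-tested diary it says that "color and consistency of the stool as well as specific symptomatic features of the diarrheal episode were recorded using colored stickers". On the local words for diarrhea, C.1 notes: "Sub types specify bloody, mucoid and prolonged diarrheas".

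**The concern.** Because the project team does not treat, referral is its main response to a sick child found at a visit, and the wording of the trigger decides what a community fieldworker must do. Read as written, D.11 lets a fieldworker record blood in the stool, or a third week of diarrhea, and leave without any instruction to refer if the child has no fever and no sign of dehydration.

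A referral rule need not match an analysis endpoint, so the difference between D.11 and D.6.c is not in itself an error. The point is the missing trigger for two signs that the protocol itself puts in its severe and persistent group. For blood, the protocol's background also gives a clinical reason: B.4 cites a study that "investigated the etiology of bloody diarrhea and identified a bacterial agent in 41% of the 133 cases". Those were patients from three cities, cited among hospital-based studies, so the share in village children may differ.

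**Working it through.** The protocol states no figure on this point, so the check is mainly a comparison of text. Arithmetic serves only to show scale.

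**Signs compared**

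| Sign | D.11 referral | D.6.c severe/persistent analysis | D.4 definition |
|---|---|---|---|
| Fever | yes | yes | – |
| Dehydration | yes | – | – |
| Blood in stool | – | yes | yes (one motion suffices) |
| Episode over 14 days | – | yes | yes (persistent) |

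The last two rows have no entry under referral, and no other symptom-based referral rule appears in the protocol text.

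**Does another route close the gap?** D.6.g and E.5 provide for treatment after a stool test result. That depends on a laboratory finding. D.5 plans it for 220 of 660 children (33%) at baseline, first episode and month 6, which leaves 660 − 220 = 440 children (67%) outside it. E.5 gives about 250 baseline samples and about 250 symptomatic ones, which still does not cover every episode.

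**Are the signs observable?** Blood must be known to apply the D.4 definition, and both signs must be known for the D.6.c analysis. Duration can be followed through daily diaries and 52 weekly visits.

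**Ceiling for blood.** Inputs: 660 children, 330 per arm (D.1). From B.4: "The same source reports a two-week prevalence of bloody diarrhea of 4.4% in urban and 7.7% in rural settings", and a rural two-week prevalence of any diarrhea of 28.7% (1994 national survey of under-fives). B.4 does not make the denominator of the 7.7% certain, so both readings are shown. The second line of each applies the one-third reduction of D.8 to the SODIS arm.

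- Reading A, 7.7% of all rural under-fives:
  - 660 × 0.077 = 50.8
  - 330 × 0.077 + 330 × 0.077 × 2/3 = 25.4 + 16.9 = 42.4 (from unrounded terms)
- Reading B, 7.7% of those with diarrhea: 0.077 × 0.287 = 0.0221
  - 660 × 0.0221 = 14.6
  - 330 × 0.0221 + 330 × 0.0221 × 2/3 = 7.3 + 4.9 = 12.2

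These are ceilings, because children who also have fever or dehydration are already referred. The share with neither sign is not in the protocol. Assuming 10–50%:

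- lowest: 0.10 × 12.2 = 1.2 children per two weeks
- highest: 0.50 × 50.8 = 25.4 children per two weeks

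For episodes over 14 days the protocol gives no frequency, so no figure can be formed.

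**The case against.** The strongest reply is that D.11 sets a minimum and forbids nothing. Staff may refer for other reasons, care is free, and where a non-treating surveillance team puts its threshold is a judgment. The weekly questionnaire sits in Appendix J, which is not available here and may hold further prompts. The clinical case is also thin: a detection rate in hospital-based patients does not show that an afebrile, hydrated village child needs referral, and for long episodes the protocol offers a definition but no evidence of harm. The information is less ready than it looks, since the D.6.c list for the weekly visit does not name blood, the diary description comes from a pre-test, and the choice of local terms was still open. The range of 1 to 25 rests on an assumed share.

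Much of this stands as a limit. No care is withheld, the range is not evidence of how many children are affected, and the clinical team should confirm the added signs. It does not remove the point. A rule that spells out its trigger will be followed as spelled out, permission to refer is not an instruction to refer, and an unseen form cannot be assumed to override the protocol text. Blood and duration have to be captured in any case for D.4 and D.6.c.

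**Conclusion.** The concern holds and is minor. Followed as written, D.11 gives no referral trigger for visible blood or for diarrhea beyond 14 days when fever and dehydration are both absent. The size cannot be derived. For blood the ceiling is about 51 (or 42) children per two weeks on one reading of the survey figure and about 15 (or 12) on the other. The range of 1 to 25 without a trigger depends on the assumed 10–50% share and on a 1994 national rate applying to these villages. The judgment covers the D.11 wording only, since the field form is not available. The primary outcome, power and arm comparison are not affected.

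**What to change.** Add two signs to the D.11 criteria, subject to confirmation by the clinical team: visible blood in the stool, and an episode lasting more than 14 days. Establish duration from the diary and earlier weekly visits, counting from onset and restarting after three diarrhea-free days as in D.4. Mark each health-provider visit that follows a project referral, so that the secondary outcome on provider visits in D.5 can be read with and without them. Leave the D.6.c analysis as it is.

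The cost is two added signs, simple tracking of duration across visits by the community fieldworkers, and one extra data mark. The downside is some additional referrals to health posts whose service is often interrupted, and some project-prompted visits in the provider-visit outcome. The sample size does not change.

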## E. Human Subjects

This protocol has been developed applying the principles of the Helsinki Declaration (last updated 1983) and adheres to the outline for Good Epidemiologic Practice of the European Epidemiology Group (1999). The protocol has been approved by the Berkeley Committee for the Protection of Human Subject, OHRP IRB number 00000775 (February 27th 2003), by the Swiss ethical research board in Basel (Ethikkommission Beider Basel) OHRP IRB number 00003565 (March 11th 2003) and by the University of San Simon IRB, Bolivia OHRP IRB number 00003509 (April 19, 2004). The protocol and has been read and approved by the local partner institutions incl. the Fundación SODIS by PCI/Bolivia. The letters of institutional clearances are attached (Appendix C).

### E.1. Study population

A total of 22 rural Bolivian communities (villages), eleven in the intervention arm and eleven in the control arm, will be enrolled from the area of operation of the a local, US-funded NGO Project Concern International (PCI). The PCI program on community development disseminates the SODIS technology to communities unsuitable for well-sinking or gravity water supply in the Cochabamba area, Bolivia. The PCI Program disseminates the SODIS intervention to whole communities, rather than to individual households or single individuals. In total 660 children under five years of age will be recruited into the study; 30 subjects from each of the 22 communities. Participating households will be recruited during the initial project period and subjects will be followed for twelve months.

Study participants will be selected based on the inclusion criteria indicated below, but only if full parental consent has been granted i.) for the household to participate in the SODIS program and ii.) to perform all project activities including water quality monitoring in the household and specimen collection of children's stools and iii.) to interview mother/caretaker (\*) of the child. A consent form will be signed by both parents and all household members. (\* Note: the closest caretaker of the child will be contacted as respondent only if the team cannot locate the mother after two unsuccessful visits to the home)

For this study we will adopt a community (cluster)-randomized controlled trial design. I.e., the implementation plans for the SODIS component of PCI program allows us to introduce SODIS in 22 communities in a random fashion determined by us. Twenty-two villages will be randomly selected from among those districts designated by PCI to receive the SODIS intervention. The SODIS intervention will be randomly assigned to eleven of the villages (the "treatment arm") whilst the remaining eleven villages serve as controls for the period of the field trial (12 months). Control communities will receive the SODIS intervention subsequently to the trial's end according to the implementation plans of PCI program.

A cohort of 660 children <5 years, 30 in each community, will be followed and monitored for the occurrence of diarrheal diseases. For the 12-months period of the trial, data on diarrheal illness will be obtained from daily morbidity diaries kept by mothers/caretakers and through weekly home visits by our project staff. Participating mothers/caretakers of the participants will also be interviewed at enrollment, and with a more detailed questionnaire twice during and once at the end of the study.

Stool samples will be collected from a random sample of children during the baseline morbidity surveys. The same children will be asked to provide one more sample at the time of their symptomatic diarrheal illness during follow-up. Water quality monitoring of raw water sources used for drinking water and of water samples after treatment with the SODIS device will be conducted systematically. Mothers/caretakers of participating children will be interviewed at baseline and repeatedly during the trial with regard to current water management, behavioral and environmental exposures of their child in the household and within the community.

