## D.2. Inclusion criteria

Subjects: Families with children <5 eligible for the study are eligible to participate if they:

- i) live permanently in the village;
- ii) consistently use unprotected drinking water sources;
- iii) give informed consent;
- iv) Children <5 years must be permanently living with their family. In households with more than one child <5 years all the children will be enrolled.

Village clusters are selected from village profiles available from PCI. They apply the following criteria to include communities within the SODIS Program:

- i) the village has no treated or improved individual- or functioning communal improved water supplies ;
- ii) the village anticipates no drinking water interventions other than those of the Latin American SODIS program (as documented by village water and sanitation development plans and discussion with the municipality or other NGOs;
- iii) uniform support for study participation is expressed by the village leadership.

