#### D.6.d. Estimation of diarrheal disease preventive fraction of child-diarrheal illness.

Applying the definition of Last, community effectiveness is defined in this setting as the impact of the SODIS intervention on the overall incidence rate of child diarrhea in the community (Last 1995). It can be expressed in two ways:

- i.) The relative risk (the ratio of the risk of diarrhea in the intervention group to that in the control group). With this ratio the community protective effect ( $CPE = (1-RR) \times 100$ ) can be obtained which expresses the percent reduction in the overall diarrheal incidence rate as a result of the SODIS intervention.
- ii) The number of diarrheal illnesses averted as a result of the intervention (attributable risk) is measured by the difference in incidence density rates between the two study groups. To obtain an absolute number of diarrheal illnesses prevented by the use of SODIS, we multiply the attributable risk with the number of diarrheal cases obtained from the cross-sectional study. (In this calculation we assume that the results from the 22 cross-sectional studies represent the frequency of diarrheal illness in the general population).

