#### **E.4. Screening**

Households with children <5 will be known from the PCI community profiles and from the screening survey. Thirty households will be randomly selected from this data base. These households will be visited by a member of the study team and the inclusion criteria assessed. To become a study participant a child under the age of five must fulfill the following criteria:

- i.) the family must be living permanently in the village
- ii.) both parents and all other adult household members must agree to participate in the study.

All the children <5 years resident in the household will be enrolled.

All information collected from households which are not eligible or decline from participation in the study will be destroyed except information on exclusion. This information will be used to assess potential biases that might occur from the selection procedure of study subjects. These data will be coded and recorded with no identifying information on the household.

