#### **E.5. Procedures**

(Note: No instructions or additional training in application and use of the SODIS device on part of the project will be given in villages in the intervention arm. Standard introduction of the device through PCI and the Fundación SODIS is a prerequisite for this effectiveness trial and will not be altered for the purpose of the study.

In summary, the SODIS device will consist of a translucent plastic bottle, which is filled with surface water collected for drinking water. The exposure of this bottle to sunlight and radiation for five hours during midday is sufficient to reduce most waterborne micro-organisms by more than 99.% and does not effect the chemical composition of the water. The PCI program introduces the SODIS device to all villagers within a community.)

Once the household consents to participate in the study the mother/caretaker of the study child will be introduced to a simple calendar chart to record the occurrence of a diarrheal episode individually for the study child and all other household members on a daily basis. This form also includes questions regarding water consumption and water management at the household. Information on type of water used, location of water sources and temporal absence of the study child from home will be collected. A community based field worker will visit the household once per week and inquire about the occurrence of gastrointestinal discomfort using an array of symptoms. These questions will be only referred to the study child. He/she will also complete an observational protocol recording environmental factors in the community and the homestead (presence of animals, cleanliness of household yard, water storage).

The mother/caretaker of the study child will also be asked to participate four times in a questionnaire-based interview. Household-based information will be collected on socio-economic situation, water handling and consumption practices, and perception of water quality. Information referring to the study child include nutritional, behavioral (water contacts, playing), and sanitary (personal hygiene, stool disposal) aspects as well as questions on health seeking and perceived health of the mother/caretaker. No such questions will be asked about other household members.

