#### **E.9. Informed consent**

Informed consent to participate in the trial relates to the diarrheal disease monitoring and the collection of stool specimen and household water samples only. The community will have consented to the introduction of the SODIS intervention prior to the trial through their interaction with implementing agency.

If a household, i.e. the parents of the study child and all other household members is willing and eligible to participate in the randomized intervention trial the project staff (representative from Centro del Aguas y Saneamiento Ambiental, LABIMED, PCI and the Swiss Tropical Institute) will provide the consent form to the parents of the study child and all household members. The form will be read and explained to them (literate guardians must read the form). Adequate time will be given and the project representative will be available to answer questions. Both parents must read and sign the form in front of a witness of the community. Consent will also be obtained from all other household members. Repeated home visits will be done to obtain all signatures. Other household members will only participate in maintaining the household morbidity calendar. They will not be asked to fill out any documents or data forms, nor will they be interviewed or have stool samples collected from them. All consent forms are attached (Appendix M).

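### Protocol E.1 makes household consent to the SODIS program an entry condition that E.9 contradicts and D.2 and E.4 omit; if applied, the community effect may be overstated

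*Protocol*

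**What the plan says.** E.1 selects participants on criteria given later in section E and then adds a proviso: "only if full parental consent has been granted i.) for the household to participate in the SODIS program". Items ii.) and iii.) follow, covering project activities (household water monitoring, stool collection) and interviews with the mother or caretaker. Consent to SODIS is therefore a separate item and not loose wording for consent to the study.

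Other sections of the protocol read differently:

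- **E.9** on the scope of trial consent: "Informed consent to participate in the trial relates to the diarrheal disease monitoring and the collection of stool specimen and household water samples only". On who accepts SODIS: "The community will have consented to the introduction of the SODIS intervention prior to the trial through their interaction with implementing agency".
- **E.4**, the list that E.1 points to: "both parents and all other adult household members must agree to participate in the study". SODIS is not mentioned.
- **D.2**, among the criteria for families: "give informed consent". SODIS is not mentioned here either.
- **E.5** on delivery: "The PCI program introduces the SODIS device to all villagers within a community". The same section says that the implementing agencies' standard introduction is not changed for the study.
- **D.6.d** on the target: "community effectiveness is defined in this setting as the impact of the SODIS intervention on the overall incidence rate of child diarrhea in the community".

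**The concern.** The Project Summary sets out to learn how much of the efficacy of SODIS survives under program conditions. The introduction to the revised application faults the Kenyan trials for leaving out ordinary inconsistency of behaviour. Families who do not want SODIS are part of the community whose incidence D.6.d describes. Field staff who apply E.1 as written would leave those families out of the cohort. Staff who apply E.9, D.2 or E.4 would keep them in, provided they accept the monitoring.

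The community protective effect, the episodes averted (which D.6.d carries over to the general population) and the cost per episode averted in D.6.e would then be estimated in households that agreed to SODIS but stated for the community. This cannot be repaired in the analysis: under D.6.a and E.4 only the information on exclusion is kept for decliners, so their diarrhea rate is never observed.

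**Working it through.** **1. Which rule applies.** E.1 requires household consent to SODIS. E.9 says that trial consent covers monitoring and samples only. D.2 and E.4 list consent or agreement to the study and nothing about SODIS. No section says which of these prevails, and the eligibility and consent forms (Appendices J and M) are not in the document. The protocol therefore has no single answer on who may enter.

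**2. Who is lost if E.1 is applied.** Only households that would decline SODIS but accept the study. Households that decline both are lost under any of the four sections. The condition makes no distinction by arm. By the order of tasks, enrolment (D.6.a) comes before the eight-week baseline survey and the allocation of villages (D.6.b), so consent appears to precede randomisation.

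**3. Inputs.**

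- Control rate 5 and intervention rate 3.33 episodes per child-year (D.8). Planned reduction: (5 − 3.333)/5 = 33.3%.
- Share f of households refusing SODIS: not given, so a range is assumed. The nearest figure is in C.1 iv.), where 142 families enrolled in the pilot and two declined: 2/144 = 1.4%. They declined the study, not SODIS, so this is a proxy only.
- Assumptions: refusers gain nothing from SODIS and have the same background rate as consenters.

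**4. Community effect when the consenting cohort shows 33.3%.** The rate in intervention communities is (1 − f) × 3.333 + f × 5, so the community reduction is 33.3% × (1 − f) and the overstatement is 33.3% × f.

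| f | Community rate | Community reduction | Overstatement (points) |
|---|---|---|---|
| 1.4% | 3.36 | 32.9% | 0.5 |
| 10% | 3.50 | 30.0% | 3.3 |
| 20% | 3.67 | 26.7% | 6.7 |

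Under these assumptions each overstatement is an upper bound on what the clause adds. Part of f would decline the study anyway, and enrolling on E.9's basis would not bring those households back.

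**5. Whether the trial can afford to keep these households.** The formula in D.8 reproduces the plan's figure. At k = 0.2 and 10 person-years per village, 2 + (1.96 + 0.84)² × {(5 + 3.333)/10 + 0.04 × (25 + 11.11)}/1.667² = 8.43, rounded up to the stated 9 villages per arm. Inverting it for 11 villages per arm with 30 person-years each and k = 0.2 gives power of 96.8% at f = 0, 96.3% at 1.4%, 92.2% at 10% and 84.1% at 20%. At k = 0.3, the upper value that D.8 allows for, the figures are 75.9%, 74.5%, 65.5% and 54.2%. That column starts below 80% whatever is done about E.1.

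**The case against.** The strongest reply is that this is one stray clause. E.1 itself refers to the criteria in E.4, which do not mention SODIS, and D.2 and E.9 agree with E.4. Three sections to one suggest that sites would not screen on willingness to use SODIS. Communities have already agreed to receive SODIS, village leaders must support the study, and the pilot saw almost no refusals. On that view the matter is minor. Much of this stands: E.1 is not shown to be the settled rule, and at the pilot's level the overstatement is about half a percentage point. But the pilot families declined a survey and not SODIS, and a rule on entry and consent needs one wording before enrolment.

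A reader might infer more than the documents support:

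- **That the trial could not measure community effectiveness at all.** Agreeing to join a program is not the same as using it. No section removes non-users. Those who abandon SODIS are surveyed, and nothing takes them out of the cohort. Abandonment and partial use after enrolment still lower the measured effect.
- **That the clause biases the comparison between arms.** As worded it applies to both arms, and consent appears to come before allocation.
- **That signing up prompts early use in control villages.** D.11 says control villages know and accept their later date in any case, and nothing in the text links the clause to early use.
- **That a large inflation is established.** Refusal shares of 20% or more have no support in the documents, and the arithmetic counts families who would refuse the study as well.

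The protocol also keeps exclusion information to assess selection bias. That can show that refusal occurred, but it cannot recover the community effect.

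**Conclusion.** The concern holds as an unreconciled contradiction about entry and consent, with a possible upward bias in the community effect if E.1 is the version applied. The issue is whom the result describes, not the validity of the randomised comparison. On the assumptions of no benefit and equal background rates among refusers, the overstatement of a 33.3% effect is at most about 0.5 points at the pilot's proxy, 3.3 points at 10% refusal and 6.7 points at 20%. The true refusal share is unknown. If refusers had a higher background rate than consenters, the equal-rate figures would no longer be a bound.

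**What to change.** Delete item i.) from E.1, and any matching line in the consent form, so that enrolment rests on consent to monitoring, interviews and samples, whether or not the household intends to use SODIS. E.9 does not name the interviews, so items ii.) and iii.) of E.1 should stay and E.9 should mention them. Record stated willingness to use SODIS at baseline as a descriptive item.

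If the sponsor wants to keep item i.), then D.2, E.4 and E.9 should be made to agree with it, SODIS refusals reported by village and arm, and the conclusions in D.6.d and D.6.e limited to consenting households.

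The cost is a wording amendment to the ethics boards and one added baseline question. The measured effect may be slightly smaller because unwilling households stay in, with the modest loss of power shown above at k = 0.2 and refusal up to 10%.
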